**Figure 1 F1:**
[figure not shown]
PALS study flow diagram. GENIE, Generating Engagement in Network Involvement; PALS, Project About Loneliness and Social networks.

### Sample size consideration

The sample size calculation is based on the primary analysis of the comparison of intervention and control arms on SF-12 Mental Health composite scale (MCS) score at 6 months,^30^ and accounts for possible intracluster correlation (ICC) within facilitators. The MCS compares an individual score with an age group mean score; a negative score reflects poorer health. Previous studies (although in different populations) have suggested that differences of 3 and 4.7 points on the SF-12 would be clinically meaningful.^31 32^ We have based the current sample size on being able to detect a difference of 4 points. Based on a previous study in socially isolated older people,^33^ we estimate the SD of the outcome to be 10.4 (using a pooled estimate of baseline scores). Choosing 80% power and a type I error rate of 5%, an individually randomised study would require 216 people (108 per arm). Regarding clustering, previous studies have generally shown low ICCs for mental health scores from SF-12 and SF-36 (0.032 and below, although for different populations and clustering within GP practices)^33 34^; we use an ICC of 0.05 here. Based on discussions with participating organisations, it was agreed that 12 participants per facilitator was suitable; this results in a design effect of 1.55 and an adjusted sample size of 335 people. Assuming 15% drop-out,^35^ we require 394 participants in total (197 per arm). This requires 33 facilitators; we will increase this to 36 facilitators to account for potential drop-out of facilitators.

### The facilitated social network intervention

The intervention process is introduced initially via a guided discussion with a trained facilitator, takes 30–40 min to deliver and has three stages: social network mapping, tailoring of preferences and linking users to valued resources and activities. By design, Genie (https://pals.genie-net.org/eng/), can be applied to varied user groups.^27^ It is based on evidence of social network properties and types, mechanisms and work relating to managing health and wellness.^36–39^ Previous testing of the principles has shown that it is both appropriate and acceptable to implement for individuals with a long-term condition.^26–28^

#### Facilitators

Guided facilitation is an important element of the guided process to using the tool. Facilitators do not need a specific in-depth theoretical knowledge: instead, the local knowledge of facilitators is important and adds to the value of the intervention. However, the interpersonal skills of the facilitator are vital for the success of engagement through promoting a collaborative solution, and engaging participant focus, motivation and reflection on social network composition and promoting new community engagement.^27^ Facilitators receive a minimum of a half-day training from the research team, which may be refreshed over the course of the study. This will include a background to, demonstration of and practical pair-working exercises using video guides around the facilitation process. Research methods training and discussion around loneliness and isolation are also addressed. The research team will provide ongoing support to monitor fidelity to the intervention deployment and address issues arising regarding complex cases (or facilitator difficulties and distress).

#### Social network mapping

Facilitators guide participants to create a visual map of their current support network, using a concentric circles method.^27^ The concentric circles process provides insight into the user’s current situation regarding social support; who they view as important in their daily lives (this may include family members, friends, acquaintances, healthcare professionals, local groups and pets); and then to reflect on renegotiating existing roles and responsibilities, and further map people and groups who could provide extended support.^26–28^ This process, when guided by the facilitator, helps the participant to realign thinking about their relationships (and conceptualise themselves within a network of support), explore family dynamics and recognise ‘weak ties’ (ie, social acquaintances) that already exist in their network.^27^ It also offers the opportunity to begin discussions about how support may be extended within the network.

#### Linking individuals with preferences and valued local and online activities and resources

The next step involves facilitating access to local resources based on personal preferences, and acceptability to encourage engagement with personal choices, through a set of 13 questions.^40^ The questions generate a set of preferred local and online resources (linked to a precreated database of categorised local organisations and resources). The facilitated discussion of preferences is linked to available and accepted potential support from people in a person’s network. Personalised results are presented in a user-friendly way aided by Google maps with clear details about access. Previous work has highlighted that this is often new and previously unthought about information for participants.^27^ The network maps, description of individual networks, preferences and the local and online resources identified as relevant by individuals can be printed to keep or reaccessed online later via a personalised Genie page.^40 41^ Two weeks after the intervention, all Genie users receive a phone call from the facilitator and alternative or additional engagement activities are discussed. The follow-up call takes up to 10–15 min.

#### Wait-list control group

All participants allocated to the control group will be offered the opportunity to use the Genie intervention with a facilitator once the 6-month follow-up has been completed to avoid increasing inequalities as a result of the study, particularly for participants living in marginalised and deprived domestic situations.

#### Patient and public involvement

Several of our partner organisations were involved in the development of the study and protocol, particularly contributing to understanding methodological issues around identifying participants. We will continue to work closely with all stakeholders in a pragmatic and flexible way to assess implementation issues throughout the study. Patient and public involvement (PPI) representatives were consulted in the development phase of the study, as well as discussion with the CLAHRC Wessex Wiserd group, and prior Genie engagement work. In addition, further PPI representatives have been included in the trial management group, and we have consulted with the user-led McPin organisation, who are represented on our Steering committee. We will involve our PPI representatives in the interpretation of the findings from our studies, particularly those of user views.

### Outcomes

The primary outcome of the trial will be the SF-12 MCS score at 6-month follow-up between the intervention and control group using a mixed-effects model (accounting for clustering within facilitators and organisation).

Secondary outcomes will includeSF-12 MCS score between the intervention and control group at 3-month follow-up.SF-12 Physical Health composite score between intervention and control groups at 6-month follow-up.Loneliness between intervention and control groups at 3-month and 6-month follow-up measured using the De Jong Loneliness scale^42^ and the Campaign against loneliness measure.^43^Social isolation between intervention and control groups at 3-month and 6-month follow-up measured using the Duke Social Support index.^44^Well-being measured using Warwick Edinburgh Mental Well-being scale.^45^Participant engagement with new activities.

Economic evaluation measures will includeQuality-adjusted life year (QALYs) (incremental QALYs) between intervention and control at 6 months, with health-related quality of life calculated using the SF-6D utility algorithm (derived from SF-12 data).^46^Incremental costs of public sector resource between intervention and control at 6 months.Cost utility (expressed in terms of cost/QALY and cost/year of sufficient capability).Capability well-being measured using the ICEpop CAPability Measure for Adults (ICECAP-A) scores between intervention and control at 6 months.^47^

Process evaluation measures will includeParticipant perceived collective efficacy measured using the Collective Efficacy in Networks Scale^48^ and social support using the Social Provisions Scale (SPA).^49^Perceptions of loneliness measured using a modified version of the Brief Illness Perception questionnaire.^50^

Intervention group onlySocial network composition change measured using Genie social network mapping (intervention group only at 3 months).

### Study endpoints

At 3 and 6 months after enrolment in to the study, patients will be invited to complete follow-up assessments. They may do this independently or with the assistance of the facilitator or a research team member (which may include online, on paper or over the phone). All follow-up assessments will be recorded no earlier than 2 weeks before the follow-up date and no later than 6 weeks after the follow-up date.

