### Randomisation

To overcome potential issues of contamination (where a facilitator could become familiar with how GENIE works and thus find out about local activities and advise control group participants), facilitators will be 1:1 randomised to either the intervention or control arm. Randomisation will be stratified by organisation in blocks of two (ie, one facilitator will be randomised to the intervention arm and one to the control arm) and carried out by the trial statistician (SE) using the statistical software R v3.5.1. In some organisations, the risk of contamination does not exist (eg, where the only contact between a facilitator and participants would be by delivering the intervention). In these cases, some efficiency is gained by randomising the participants individually (block randomised 1:1 to intervention and control, again stratifying by organisation). The summary below details the different scenarios. Preferred options (A&B) to be used whenever possible: Randomise facilitators and participantsIntervention facilitators only to be trained

If there are organisational or setting constraints which prohibit facilitator or participant randomisation (eg, the facilitator works within a specified geographic location) we will assess whether there is ongoing contact between the facilitator and potential participants. In these scenarios: Where there is ongoing contact (C)Train intervention facilitators onlyRandomise facilitators onlyParticipants within each area allocated to facilitator (not randomised)Where there is no ongoing contact (D)Train all facilitatorsRandomise participants

**Table 1 T1:** The factors affecting the recruitment and randomisation process

Participant recruitment	Contact between participant and facilitator	
	Ongoing	One-off contact (at facilitation)
Area/location not restricted	MODEL B Randomise facilitators and participants Intervention facilitators only to be trained	MODEL A Randomise facilitators and participants Intervention facilitators only to be trained
Within a specific geographical (or other prespecified) area	MODEL C Train intervention facilitators only Randomise facilitators only Participants within each area allocated to facilitator (not randomised)	MODEL D Train all facilitators Randomise participants

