### Participant flow through the study

Written informed consent will be collected from all participants and baseline data collected with a research team member (online or on paper, dependent on the participant preferences). Allocation will occur once the baseline assessment has been completed. Participants who are allocated to the intervention condition will be given access to the Genie intervention within 2 weeks of the baseline appointment; this process will be guided by the facilitator at a location to suit them (ie, at home or in the community). At 3 and 6 months after enrolment into the study, participants will be invited to complete follow-up assessments. All follow-up assessments will be recorded no earlier than 2 weeks before the follow-up date and no later than 6 weeks after the follow-up date. Each participant will be sent a £10 high street gift voucher with the 6-month follow-up questionnaire. Individuals allocated to the control group will be offered access to Genie with the facilitator after the have completed their 6-month follow-up assessment. Participant flow is outlined in figure 1.

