### Measures

See table 2 for full details of study measures.

**Table 2 T2:** Measures and schedule of observations within the PALS study

Measure	Time point (month)		
	Baseline	3-month follow-up	6-month follow-up
Sociodemographic measures	X		
Patient self-report measures (both groups)			
SF-12 Mental Health	X	X	X
SF-12 Physical Health	X	X	X
Loneliness (De Jong Scale)	X	X	X
Social isolation (Duke Social Support index)	X	X	X
Campaign to End Loneliness scale	X	X	X
Collective Efficacy in Networks Scale (CENS)	X	X	X
Social support (SPA)	X	X	X
Warwick Edinburgh Mental Well-Being Scale (SWEMWBS)	X	X	X
Perceptions of loneliness (modified B-IPQ)	X	X	X
Participant engagement with new activities	X	X	X
Patient measures (network mapping, intervention group only)			
Social network composition change	X	X	
Economic measures			
SF-6D	X	X	X
Capability well-being (ICECAP-A)	X	X	X
Health and social care use	X	X	X
Process evaluation			
Qualitative interviews with participants	X	X	X
Qualitative interviews with facilitators and stakeholders	X	X	X
Observations of facilitation	X		
Community staff observations of impact	X	X	X

PALS, Project About Loneliness and Social networks.

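### The facilitator who delivers Genie may help participants complete the self-reported 3- and 6-month outcomes, an avoidable risk of arm-dependent reporting bias in the primary SF-12 MCS comparison

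*Protocol article*

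**What the plan says.** The protocol article's Study endpoints section covers how the 3- and 6-month assessments are completed, including online, on paper or by telephone: "They may do this independently or with the assistance of the facilitator or a research team member". It does not limit this by arm, by type of item or by whether the facilitator delivered the intervention.

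Other sections describe the facilitator's role:

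- **Delivery.** Participant flow through the study says of Genie access in the intervention arm that "this process will be guided by the facilitator at a location to suit them".
- **Follow-up call.** The section on linking individuals with activities and resources adds that two weeks later "all Genie users receive a phone call from the facilitator".
- **Controls.** Under Wait-list control group, controls are "offered the opportunity to use the Genie intervention with a facilitator once the 6-month follow-up has been completed".
- **Training.** In Models A to C of the Randomisation section the rule is to train the intervention arm's facilitators alone ("Intervention facilitators only to be trained" in Models A and B). In Model D all facilitators are trained and participants are randomised.
- **Baseline.** Participant flow has "baseline data collected with a research team member" and does not name the facilitator.

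Table 2 lists SF-12, loneliness, social isolation and well-being as self-reported in both groups.

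**The concern.** SF-12 MCS and the loneliness, isolation and well-being scales are subjective, and Genie participants know they have used it. Who sits with the participant at follow-up is one of the few influences on reporting that the design can still control. The permission lets that person be the one whose work is being judged. A control participant cannot be in that position before the 6-month assessment.

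A participant may report better mood to someone who has tried to help. That is plausible, but it is an assumption; the document gives no evidence on it. If it happens, the shift enters the primary comparison directly. It would also reach the economic evaluation, because SF-6D utilities and QALYs are derived from the same SF-12 answers. More participants would not reduce it.

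**Working it through.** **1. Is the permission the same in both arms?** In wording, yes. In effect, no.

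| | Genie arm by 6 months | Control arm by 6 months |
|---|---|---|
| Models A and D (one-off contact) | Facilitator has delivered Genie and telephoned | No Genie contact with a facilitator yet |
| Models B and C (ongoing contact by the setting or area model) | Trained facilitator has delivered Genie and telephoned | May know a facilitator, but an untrained one who has not delivered Genie |

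In Models B and C the difference lies in having delivered Genie, not in having a facilitator.

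**2. Does it fit the Randomisation section?** Individual randomisation is justified there by settings without contamination risk, for example "where the only contact between a facilitator and participants would be by delivering the intervention". Facilitator help with questionnaires is a further contact. Either facilitators do not help in those settings, or the premise does not hold there. In Model D, where every facilitator is trained, helping a control at 3 months would put a trained facilitator in touch with that control before the primary endpoint. This could dilute the effect, which is one reason the net direction is not certain.

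**3. Does the planned model remove it?** The primary model has facilitator and organisation random intercepts and adjusts for baseline SF-12. Random intercepts describe variation between facilitators; they do not remove a systematic shift in one arm. Baseline was taken with a research team member, so it does not carry the same influence. Assistance arises after randomisation, so adjusting for it later would not restore the randomised comparison.

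**4. Planned precision.** Inputs from Sample size consideration: difference 4, SD 10.4, 80% power, 5% type I error, ICC 0.05, 12 participants per facilitator, 15% drop-out.

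- Two-sided t-test: 107.09, so 108 per arm, 216 in total (as stated).
- Design effect: 1 + (12 − 1) × 0.05 = 1.55 (as stated).
- 216 × 1.55 = 334.8, so 335 (as stated).
- 335 / (1 − 0.15) = 394.1 (stated 394).

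The sample size reproduces and is not in question. The implied standard error of the difference is

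SE = √(4 × 10.4² × 1.55 / 335) = √2.002 = 1.415 points.

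**5. Illustrative size.** Let f be the share of the Genie arm helped by its facilitator and b the shift in reported MCS among those helped, with no shift in controls. The document gives neither f nor b. Then

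bias d = f × b

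false-positive rate = 1 − Φ(1.96 − d/SE) + Φ(−1.96 − d/SE).

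| f | b (points) | d (points) | d as % of 4 | Two-sided false-positive rate |
|---|---|---|---|---|
| 0.10 | 2 | 0.2 | 5% | 5.2% |
| 0.10 | 4 | 0.4 | 10% | 5.9% |
| 0.25 | 2 | 0.5 | 12.5% | 6.4% |
| 0.50 | 2 | 1.0 | 25% | 10.9% |
| 0.50 | 4 | 2.0 | 50% | 29.3% |

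If control facilitators also help and produce a similar shift, d shrinks towards zero.

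**The case against.** The permission is optional and open to both arms, and research-team help stands beside it. Few participants may use the facilitator. Read literally, the one-off contact settings would have no facilitator present at follow-up in either arm, so help is most likely under ongoing contact, where controls have facilitators too. Both inputs to the size calculation are assumed, and the 29% figure joins the two upper values. Some reporting bias is inherent in an open wait-list comparison with self-reported outcomes, and removing the facilitator takes away only an increment. A familiar helper may also keep isolated people in a study that allows for 15% drop-out. Finally, the research team trains and supports facilitators, so a helper unaware of allocation may need staff the article does not describe.

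Most of this stands, and it limits the claim. A reader might infer that bias towards Genie is built into the trial, or that controls never have a facilitator. The article supports neither: help is optional, its uptake and effect are not given, and Models B and C can give controls a facilitator.

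What remains is that the permission is positively stated, nothing in the article narrows it, and having delivered Genie by 6 months is confined to the intervention arm in every model. That recording the helper and a sensitivity analysis are not mentioned is no fault in a condensed article; they matter here only as a fallback.

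**Conclusion.** The point holds as an avoidable risk, not as a demonstrated bias. The text lets the deliverer of Genie help with the self-reported primary outcome, the asymmetry between arms follows from the design, and the planned model does not correct for it. The direction is probably towards Genie but is not certain. The size cannot be determined from the document: 0.2 to 2.0 points against the 4-point target, with a false-positive rate of about 5% to 29%, holds only for 10-50% of the Genie arm helped, a 2-4 point shift, none in controls and an SE of 1.415. With lower uptake or a smaller shift, the effect could be negligible. The conflict with the contact premise in the Randomisation section needs reconciling whatever the size.

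**What to change.** In Study endpoints, delete the facilitator from the permitted helpers at 3 and 6 months. Leave self-completion or help from a research team member who is not involved in delivering Genie, and who is unaware of allocation only where existing staffing allows. This also brings the text into line with the contact premise in the Randomisation section.

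If facilitator help cannot be avoided for some participants, record who helped at each assessment and report a sensitivity analysis excluding facilitator-assisted responses. State that this analysis cannot fully remove the bias, because who receives help is not randomised.

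The cost is one sentence in the protocol, slightly more research-team time and possibly a small loss of response among participants who prefer a familiar helper. The fallback adds one data field.

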### Measures

See table 2 for full details of study measures.

**Table 2 T2:** Measures and schedule of observations within the PALS study

Measure	Time point (month)		
	Baseline	3-month follow-up	6-month follow-up
Sociodemographic measures	X		
Patient self-report measures (both groups)			
SF-12 Mental Health	X	X	X
SF-12 Physical Health	X	X	X
Loneliness (De Jong Scale)	X	X	X
Social isolation (Duke Social Support index)	X	X	X
Campaign to End Loneliness scale	X	X	X
Collective Efficacy in Networks Scale (CENS)	X	X	X
Social support (SPA)	X	X	X
Warwick Edinburgh Mental Well-Being Scale (SWEMWBS)	X	X	X
Perceptions of loneliness (modified B-IPQ)	X	X	X
Participant engagement with new activities	X	X	X
Patient measures (network mapping, intervention group only)			
Social network composition change	X	X	
Economic measures			
SF-6D	X	X	X
Capability well-being (ICECAP-A)	X	X	X
Health and social care use	X	X	X
Process evaluation			
Qualitative interviews with participants	X	X	X
Qualitative interviews with facilitators and stakeholders	X	X	X
Observations of facilitation	X		
Community staff observations of impact	X	X	X

PALS, Project About Loneliness and Social networks.

### Statistical analysis

All analyses will emphasise estimation and CIs over hypothesis testing, and will be conducted as intention-to-treat. Missing data will be assumed to be missing at random, unless accounting for more than 10% of the sample; if missingness is above this rate, approaches for dealing with missing data (eg, multiple imputation) will be discussed within the research team. Missingness will be reported for each arm and summaries of baseline characteristics of those lost to follow-up and those not will be used to judge potential sources of bias.

Baseline sociodemographic data will be summarised within randomised arms using appropriate descriptive measures; likewise, all outcome measures will be summarised by arm at each timepoint. We will produce a forest plot of estimated effects for each outcome within each organisation to explore any variability in the impact of the intervention.

The primary analysis will involve a mixed-effects model (pending the model meeting the associated assumptions) comparing groups on SF-12 at 6 months. The model will include a random intercept for facilitator and organisation, with participants clustered within facilitators clustered within organisation (hence a three-level model) and control for baseline SF-12. This analysis will be complemented by an analysis using the same framework but with SF-12 as the outcome and a random coefficient for time, where repeated measurements are clustered within participants (hence a four-level model).

Non-response bias (ie, where a particular group of participants are unavailable or refuse to participate) will be reduced by taking steps to increase the initial response rate and reduce drop-out over the course of the study.

